### Secondary outcome measures

#### Psychological assessments—questionnaires (Table 1)

With respect to antisocial behaviour and omega-3 supplementation, the measurement of psychological change will focus on both the behavioural and the psychometric expression of aggression. Previous research [2] has used the *Aggression Questionnaire* (AQ) [45] to assess cognitive changes in aggression. The AQ is a self-report inventory that screens adults for aggressive tendencies, providing sufficient detail to enable treatment outcome measurement.

The benefits from essential fatty acid supplementation with ADHD are most likely with the inattentive subtype [54]. Recent models of attention deficit disorders (ADDs) have suggested that the core symptoms of ADDs are essentially cognitive [55]. Emotions have been identified as being one of the cognitive functions affected by ADDs, with the management of frustration and anger often impaired [56]. Such deficits are assessed by the *Brown Attention Deficit Disorder Scales* [46]. The BADDS has been used for ADD screening as well as the monitoring of treatment effectiveness of ADD and has been reported to have good construct and internal validity as well as discriminative power [57]. *Conners’* ADHD scales [47] have been well-validated and widely used in ADHD research including a range of omega-3 studies [33]. The 21-item Depression and Anxiety Stress Scales (*DASS-21* [49];) will be used to assess depression, anxiety and stress. Barratt Impulsiveness Scale (*BIS-Brief*) will be used to assess impulsiveness [48]. The Project Officers will assist in the delivery of psychological tests (*AQ*, *BADDS*, *Conner’s ADHD*, *DASS-21* and *BIS-Brief*) at baseline and post-intervention.

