### Sample size {14}

Our study is a randomised controlled trial powered to show a difference between treatment and placebo control of 25% in the proportion of participants experiencing a reduction in aggressive behaviour as measured by a change in the IBOS. Given the nature of the prison populations, it is likely that there will be an effect of prison in the analysis, and therefore, a design effect accounting for the intra-cluster correlation is incorporated in the sample size estimation with a conservatively estimated ICC of 0.03. Based on our pilot data, we anticipate that attrition will likely be high (~ 40%) with the sample size for recruitment appropriately inflated to account for this. Overall, a total sample size of 600 with 360 completing the study enables a difference of 25% to be detected with 80% power and an alpha level of 0.05.

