### Methods for additional analyses (e.g. subgroup analyses) {20b}

A priori, a subgroup per protocol analysis is planned for those participants deemed to be compliant with treatment. Subgroup analysis that will be considered include 80% compliance to capsule regime, age as a covariate, per change in omega-3 as recommended by the ISSFAL [24] and the Aggression Questionnaire—high vs low dispositional aggression.

The covariates that might be adjusted for include baseline DASS scores and SF-36 scores. It is acknowledged that reactive aggression is influenced by depression, anxiety and stress and this will be identified through the DASS. The dispositional ‘satisfaction’ will be assessed via the SF-36. With respect to ADHD, we hypothesise a mediating role of ADHD in aggressive behaviour.

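### The Aggression Questionnaire subgroup analysis is framed only as a two-group split; the continuous baseline score would be a better main test if effect modification is graded

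*Protocol article*

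**What the plan says.** The section on additional analyses ({20b}) introduces its list tentatively: "Subgroup analysis that will be considered include 80% compliance to capsule regime". The list goes on to age, entered as a covariate, the change in omega-3, and finally the AQ, as "high vs low dispositional aggression". This is the only form given for the AQ analysis. The section names no cut point and does not say which AQ measurement defines the groups.

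Under the secondary outcomes, the article describes the instrument: "The AQ is a self-report inventory that screens adults for aggressive tendencies". It is administered "at baseline and post-intervention", and Table 1 also lists it as a secondary outcome.

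The statistical methods section ({20a}) plans generalised linear mixed models adjusted for prison, and allows generalised additive mixed models for the IBOS scores. The sample size section ({14}) sizes the trial for the main comparison only: "a total sample size of 600 with 360 completing the study enables a difference of 25% to be detected with 80% power".

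**The concern.** Whether the supplement works differently in men with a more or less aggressive disposition is a natural question for this trial. Comparing two groups treats every man on one side of the cut as alike, and treats men just above and just below it as different. If the treatment effect changes gradually with the score, this weakens the test of interaction.

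The trial has little interaction power to spare. It is sized for a main effect, and about 40% of participants are expected to drop out. An avoidable loss could hide a real gradient in benefit, or leave an estimate too imprecise to guide later work.

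The AQ is also measured after treatment and is itself expected to fall on the supplement. A grouping should therefore be tied explicitly to the baseline score.

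**Working it through.** **The plan's own figure.** The protocol gives no power or information figure for the AQ subgroup, so only the main sample size can be reproduced.
- Attrition: 360 / (1 − 0.40) = 600, as stated.
- Design effect with a "conservatively estimated ICC of 0.03" and an assumed 6 equal centres of 60 completers: 1 + (60 − 1) × 0.03 = 2.77.
- With assumed responder rates of 25% and 50%, two-sided testing at "an alpha level of 0.05" and a continuity correction, 66 men per arm are needed before clustering: 2 × 66 × 2.77 ≈ 366, close to 360. The article gives neither the responder rates, the cluster size nor the sidedness.

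So the 360 completers are taken up by the main comparison.

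**Information kept by a split.** If effect modification is linear in the score, the relative efficiency of the split is the squared correlation between the score and its two-group version. For a normal score cut at quantile q this is φ(z_q)² / [q(1 − q)].
- Median: 0.3989² / 0.25 = 2/π = 0.637.
- For a uniform score cut at its median it is 0.75.

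| Score and cut (assumed) | Efficiency | Loss | 360 acts like |
|---|---|---|---|
| Uniform, median | 0.750 | 25% | 270 |
| Normal, median | 0.637 | 36% | 229 |
| Normal, 40/60 | 0.622 | 38% | 224 |
| Normal, tertile | 0.595 | 41% | 214 |
| Normal, quartile | 0.539 | 46% | 194 |
| Normal, 20/80 | 0.490 | 51% | 176 |
| Normal, 10/90 | 0.342 | 66% | 123 |

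**Effect on power (normal score, median split).** For 80% power the continuous test needs a standardised effect of 1.960 + 0.842 = 2.802. The split reduces it to 2.802 × √0.637 = 2.235. Power becomes Φ(2.235 − 1.960) = Φ(0.275) ≈ 0.61.

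**Simulation.** There were 360 men and 4,000 trials per setting, with a continuous outcome of unit residual SD, an interaction coefficient of 0.2953 and a median split. Clustering was not modelled, so the comparison between columns matters more than the absolute values.

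| Score | True modification | Power, continuous | Power, split |
|---|---|---|---|
| Normal | Linear | 0.79 | 0.58 |
| Uniform | Linear | 0.81 | 0.68 |
| Skewed (exponential) | Linear | 0.78 | 0.46 |
| Normal | Step at cut | 0.60 | 0.78 |
| Uniform | Step at cut | 0.66 | 0.78 |
| Skewed (exponential) | Step at cut | 0.49 | 0.77 |

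The continuous test wins under linear modification for all three score shapes. The split wins under all three when the modification is a step at the cut used.

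**The case against.** The strongest reply is that half a clause is being read as a method. The AQ appears among analyses that may be looked at. The wording that marks an analysis as planned in advance is in the preceding sentence and refers to the per-protocol subgroup. A reader might infer that the protocol commits in advance to a dichotomised AQ analysis, but the text does not go that far.

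A reader might also infer that a third of the information will certainly be lost. The documents do not support that: they give no cut, distribution or shape of interaction, and under a step at the cut the ranking reverses.

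Nor do they support the inference that the cut will be chosen after seeing the data, or that each group will be tested separately in place of an interaction. The article is silent on both. These details are commonly left to a statistical analysis plan, which is not shown, so their absence is no fault.

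Finally, one can say that high versus low is a contrast of interest for a screening inventory and does not exclude modelling the full score. That is fair, and the use of the baseline score is itself an inference, though the natural one.

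These replies limit the strength of the point but do not remove it. The two-group form is the only one written down, and it is the weaker one if modification is graded. The step exception helps only if the true threshold is known, and the article offers none. The same list takes age as a covariate and omega-3 by its change, without a high/low split.

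**Conclusion.** The point holds as a cheap improvement. The stated form of the AQ subgroup analysis dichotomises a questionnaire score. If effect modification is linear, the loss is about 36% for a normal score cut at the median, within a range of about 25% to 66% over the score shapes and cuts in the efficiency table. In power terms, an interaction that the continuous score would detect 80% of the time is detected about 61% of the time after a median split of a normal score.

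All of these figures rest on assumptions about the score and the interaction, and the advantage reverses for a true step at the cut. The consequence is confined to one exploratory subgroup analysis. A reader might infer some weakness in the main result; there is none from this source, because the primary analysis is on the IBOS, by intention to treat, and does not use the AQ groups.

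**What to change.** Reword the AQ item in section {20b} so that the main test, if the analysis is done, is the treatment by baseline AQ interaction. The AQ should enter as a continuous score in the mixed model already planned for the primary outcome. State that the baseline measurement is used. Check linearity with a spline, and report the treatment effect with its confidence interval at, for example, the 25th and 75th percentiles of baseline AQ. Keep high and low groups for display only.

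The cost is a line or two of analysis text, with no new data and no change to the sample size. The price is an assumed linear interaction. The spline guards against clear departures, although with about 360 completers it will not detect subtle ones.

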### Methods in analysis to handle protocol non-adherence and any statistical methods to handle missing data {20c}

The primary analysis with be on an intention-to-treat basis. A per-protocol analysis will be performed on the subgroup deemed to be compliant with the trial protocol. Longitudinal analyses will be performed using restricted maximum likelihood, and therefore, all participants providing partial data will be included in the analysis.

### Plans to give access to the full protocol, participant-level data and statistical code {31c}

Data and blood samples will be retained for the potential to analyse additional health benefits including anti-inflammatory effects, nutritional, metabolic and oxidative markers on the cohort subject to funding. The data and blood samples will be retained for the potential use of longer term outcomes on the cohort. The State Records requirement for research data states that samples should be stored for a minimum of 20 years after the project is completed. Samples will be stored in the NSW Health Statewide Biobank in Sydney. There are plans for sharing the de-identified data, after the original researchers have completed all the data analysis and published the findings.

The NHMRC encourages data sharing and it is envisaged that the data sharing will commence after our study is completed—hence, the necessary approval from study participants for this to occur up front as to seek approval from them in the future would be impossible. The data that will be shared will be completely de-identified data.

Future use of data could include longer term recidivism outcomes. Should the researchers wish to utilise the facility of the re-identifiable dataset, they would need to consult with the custodians of that dataset, i.e. Corrections in each state.

Follow-up research could include the influence of this research on the development of policy and practice and the rollout and adherence to policy.

Data will be available after all researchers involved in this trial have finished analysing and publishing the data. Data may become available to only those researchers who provide a methodologically sound proposal, and this will be determined on a case-by-case basis at the discretion of the Principal Investigator.

Secondary analysis of data could include the link between ADHD and criminal infractions.

## Oversight and monitoring

### Composition of the coordinating centre and trial steering committee {5d}

The University of Wollongong is the coordinating centre. The Principal Investigator and the second Principal Investigator are largely responsible of the running of the research project and supervision of the post-doctoral fellow.

A steering committee comprising of all Chief Investigators and the Governors (or their nominees) from Correctional Centres will meet on a regular basis to discuss the progress of the trial for each site. A regular quarterly newsletter will be circulated to all Chief Investigators, Associate Investigators, Governors and partner organisations informing regarding the progress of the research project.

### Composition of the data monitoring committee, its role and reporting structure {21a}

Data monitoring will be undertaken by the trial management group: CIA, CIB and the post-doctoral research fellow. Given that the researchers are blind to allocation, data monitoring will occur solely to ensure data quality and adherence to the study protocol. Data monitoring in terms of recruitment rates will be undertaken by the funding bodies: the National Health and Medical Research Council and DSM Nutritional Products.

### Adverse event reporting and harms {22}

Adverse events will be collected by spontaneous report by the Project Officer. All adverse events will be reported in trial publications. Any adverse medical outcomes (it is anticipated that these, if any, will be minor, e.g. bruising after blood collection) will be recorded by the Project Officer using the Adverse Events form. The Project Officer will notify the CIA BJM of these adverse events as they occur who will discuss the adverse outcomes with CIG DG and they will react as necessary and responsibly. All adverse events will be reported to DSM when they occur and definitely at the end of the study. Usual corrective services protocols for prisoner health will continue.

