### Intervention description {11a}

The Correctional Officer on secondment as the Project Officer will deliver the supplements to the enrolled prisoners on Mondays, Wednesdays and Fridays, and they will watch participants swallow the supplements to ensure compliance. Supplements will be provided over a 16-week duration, the average supplement duration of the 2 previous studies [2, 3]. Baseline and post-intervention measures include IBOS, institutional records of reprimands or misconduct, questionnaires and measure of muscle strength, and blood samples to measure the erythrocyte omega-3 index levels will also be used as a measure of compliance. The questionnaires are demographic (in house), Aggression Questionnaire (AQ) [45]; Browns Attention Deficit Disorder Scales (BADDS) [46]; Conners’ Attention Deficit Hyperactivity Disorder (ADHD) [47]; The Barratts Impulsiveness Scale-11 (BIS-11) [48]; Depression, Anxiety, Stress Scale (DASS-21) [49]; Wellness Questionnaire - the Short Form-36 [50, 51]; plus customised questions on sleep.

The prisoners will also be asked at the end of the trial which treatment they thought they were on.

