### Strategies to improve adherence to interventions {11c}

The Correctional Officer on secondment as the Project Officer will deliver the supplements to the enrolled prisoners and watch them taking the supplements to ensure compliance and therefore monitoring adherence to the study protocol. Adherence will be recorded for each week, with reasons for a lack of adherence recorded. Changes in participant’s omega-3 levels will also be used to determine adherence to treatment.

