### Plans to promote participant retention and complete follow-up {18b}

Project Officers will routinely discuss participant experience of the trial as the capsules are delivered. In doing so, participant indication of a desire to discontinue trial engagement will be discussed and where individual problems associated with participation are identified, the Project Officer will assist the participant to problem solve a solution to enable ongoing participation.

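### Adverse events are collected by spontaneous report only, and the delivery conversations and logged reasons for missed capsules are not stated to feed the Adverse Events form, so harms may be undercounted

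*Protocol article*

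**What the plan says.** All references are to the protocol article.

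- **Adverse event reporting and harms {22}** fixes the method and then makes a promise: "Adverse events will be collected by spontaneous report by the Project Officer. All adverse events will be reported in trial publications". Adverse medical outcomes "will be recorded by the Project Officer using the Adverse Events form". The officer notifies the lead investigator, who discusses them with the medically qualified investigator.
- **Criteria for discontinuing or modifying allocated interventions {11b}** has an adverse event report from the on-site officer evaluated by that medically qualified investigator.
- **Intervention description {11a}** says the same officer "will deliver the supplements to the enrolled prisoners on Mondays, Wednesdays and Fridays, and they will watch participants swallow the supplements to ensure compliance", over 16 weeks.
- **Strategies to improve adherence to interventions {11c}** adds: "Adherence will be recorded for each week, with reasons for a lack of adherence recorded".
- **Plans to promote participant retention and complete follow-up {18b}** has the officer talk routinely with each man about his experience of the trial at delivery. If a man indicates that he wishes to stop and a problem is identified, "the Project Officer will assist the participant to problem solve a solution to enable ongoing participation".
- **Who will be blinded {17a}** covers both officers and participants.

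**The concern.** The article does not leave safety collection open. It names a method, and the method is passive: a prisoner has to volunteer a symptom to a seconded correctional officer, who has to treat it as an adverse event. Two richer sources are already in the officer's hands, namely the conversation at delivery and the weekly reasons for missed capsules. Each is described with a different purpose, retention in one case and adherence in the other. Neither section mentions the Adverse Events form.

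A man who misses capsules because he feels unwell will be in the adherence record. A man who wants to stop because of a symptom will be offered help to continue. The article does not say that either is also recorded as an adverse event. The officer's report is what leads to medical evaluation under {11b}, so an event that is not treated as one has no stated path there.

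The harms data will carry weight. Positive results are meant to support national supplementation in prisons (Translation into policy and practice), and the Discussion already describes the product as low risk. If few events are seen, a reader needs to know how far that reflects the product and how far it reflects the way events were sought.

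**Working it through.** **1. Is there a figure to reproduce?** No. The article gives no expected adverse event rate, no capture rate and no power for a safety comparison. The check is a reading of the sections together, plus arithmetic on opportunity and an illustration on assumed values.

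**2. The information streams side by side.**

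| Stream | Section | Stated purpose | Stated link to the Adverse Events form |
|---|---|---|---|
| Spontaneous report to the officer | {22} | Adverse event collection | Yes |
| Conversation at capsule delivery | {18b} | Retention | None stated |
| Weekly reasons for non-adherence | {11c} | Adherence | None stated |

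No section says that the second and third streams feed the form, and no section says that they do not.

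**3. Opportunity to ask.** Inputs: 3 deliveries a week and 16 weeks ({11a}); 600 recruited and 360 completing (Sample size {14}).

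- Per man over a full course: 3 × 16 = 48 contacts.
- For 360 completers: 48 × 360 = 17,280 contacts.
- Upper limit, if nobody dropped out: 48 × 600 = 28,800 contacts.

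A weekly question would use 16 of the 48 contacts and require no new visit.

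**4. Illustration of what partial capture costs.** The event rates and capture fractions here are assumptions and do not come from the article. Suppose true risks of 20% and 10%, with the same capture fraction c in both arms, so that the recorded risks are p1 = 0.20c and p2 = 0.10c. With n per arm and a two-sided 5% test:

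power = Φ[(p1 − p2 − 1.96·s0)/s1], where s0 = √(2·p̄(1 − p̄)/n), p̄ = (p1 + p2)/2, and s1 = √([p1(1 − p1) + p2(1 − p2)]/n).

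Worked case, n = 180 (half of 360), c = 1: s0 = √(2 × 0.15 × 0.85/180) = 0.0376; s1 = √((0.16 + 0.09)/180) = 0.0373; power = Φ[(0.10 − 1.96 × 0.0376)/0.0373] = Φ(0.70) = 0.76.

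| Capture c | Recorded risks | Power, 180 per arm | Power, 300 per arm |
|---|---|---|---|
| 100% | 20% vs 10% | 0.76 | 0.93 |
| 50% | 10% vs 5% | 0.44 | 0.64 |
| 25% | 5% vs 2.5% | 0.24 | 0.36 |

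The ratio of risks stays at 2 in every row. The recorded difference shrinks from 10 to 5 to 2.5 percentage points. Equal under-capture therefore leaves the ratio unbiased but weakens the evidence. The 300-per-arm column ignores attrition and is the more favourable case.

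**The case against.** The strongest reply is that the article's silence proves little. A man who tells the officer at delivery that he feels ill has made a spontaneous report to the very person who fills in the form. Recording the same fact as a reason for non-adherence, or discussing it under {18b}, does not stop it being recorded under {22}. The routine conversation about trial experience is itself close to an open question. Officers share a three-day training course and a manual of procedures, which is not shown and may cover this. Harms are expected to be minor, and the trial makes no claim of power for safety.

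Much of this stands, and it rules out three stronger readings that a reader might infer:

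- **That the delivery contacts and adherence log do not feed the form, or that no contact prompts for events.** The documents do not say so. What can be said is that no link and no standard question is stated.
- **That the promise to report all adverse events is contradicted.** It follows directly on the sentence about collection and can mean all events collected.
- **That the safety comparison is biased in a known direction.** Officers and participants are blinded, so under-recording should be broadly similar in the two arms.

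The reply does not remove the point itself. An unstandardised conversation held for retention is not the same as a fixed question asked of everyone. The training topics listed under Plans for assessment and collection of outcomes {18a} do not include recognising adverse events, though the manual may. An unseen manual also does not alter the collection method that the article states.

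**Conclusion.** The point holds in a limited form. Spontaneous report is the only named route for adverse events, and two existing sources held by the same officer are not stated to reach the Adverse Events form. Harms may therefore be undercounted, most likely to a similar degree in both arms. The loss is in event counts and in the precision of the safety comparison.

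The size cannot be derived from the documents. The power figures above show the direction and rough scale of the loss under assumed rates and capture fractions, and are not an estimate for this trial. The conclusion rests on blinding being maintained, and on the full protocol and manual not already containing a solicited question or an explicit link. The improvement is worth making because it is cheap and the results are meant to inform policy.

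**What to change.** In Adverse event reporting and harms {22}:

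1. Add one fixed, open, non-leading question about health, put to every participant once a week at an existing capsule delivery. Keep spontaneous reporting alongside it.
2. State that any health-related reason for a missed capsule ({11c}) or for wishing to stop ({18b}) is also entered on the Adverse Events form. This concerns recording only; how medical review and the retention conversation are ordered is for the sponsor and investigators.
3. Report adverse events by arm, with solicited and spontaneous events shown separately, and give the date on which collection changed.
4. If no change is made, describe the published events as all spontaneously reported adverse events.

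**Cost.** One line on the weekly adherence sheet, a small amendment with ethics approval where needed, and a briefing for officers at six or more centres in two states. More minor events will be recorded. Recruitment began in April 2019, so men already treated were captured passively. Their data cannot be upgraded, which is why the change date must be reported. Dose, endpoints and randomisation are unaffected.
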